**Fig. 1 Fig1:**
[figure not shown]
OMMIT-2 Prediction of adverse outcome in MC twins: prospective study

Women who develop complications are referred to the West Midlands Fetal Medicine Centre. The second cohort (Cohort C) will have serial maternal blood tests performed (pre-FLA and 6 h post-FLA) looking at the biomarkers informed by the IPD meta-analysis and retrospective study. A small amniotic fluid sample will be collected pre-FLA when the port for the fetoscope has been inserted into the recipient sac in the uterus, and a second small sample taken post-FLA when the ablation has been completed. The recipient twin will have polyhydramnios as it is part of the diagnostic criteria for TTTS, and it is routine clinical practice to perform amnioreduction at this point. All samples (serum and amniotic fluid) will be spun down, aliquoted, frozen and stored at−80° Celsius. We will assess the same factors in the amniotic fluid as in the maternal serum. Data will be collected on the ultrasound scans performed as part of routine clinical management of these conditions, as will pregnancy outcome data. Quintero staging will be used to classify TTTS [8].

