## Background

All twin pregnancies have increased risk over singletons, with monochorionic (MC) twins demonstrating the highest risk. Thirty per cent of twins are MC, but they experience 75% of all twin complications, the pathologies of which are closely linked to the fact that they share a single placenta and thus can develop unbalanced vascular anastomoses [1]. Complications that are specific to monochorionicity include twin-twin transfusion syndrome (TTTS), selective intrauterine growth restriction (sIUGR) and twin anaemia polycythaemia sequence (TAPS) [2]. TTTS complicates 10–15% of MC twins and usually occurs between 15 and 26 weeks. At present, the prognosis is dependent upon early treatment and method of treatment: if untreated it is associated with a perinatal loss rate of 70–90%. A staging system, the Quintero system, exists but correlates poorly with outcome [3]. Even with apparently ‘successful’ antenatal treatment (with fetoscopic laser ablation (FLA)), TTTS is still associated with 10% neurological morbidity. We are currently unable to accurately predict which twins will develop complications or how severe they will be. There is some evidence that first trimester ultrasound screening of MC twin pregnancies between 11 and 13^+6^ weeks may predict adverse pregnancy outcome. These ultrasound features include: a) discordance in fetal nuchal translucency thickness (NT) with an increase in the recipient fetus [4, 5] and b) discordance in fetal crown rump length (CRL) measurements between the MC twins [5]. Although ultrasonographic features have a reasonable sensitivity and specificity in terms of allocating risk of severe TTTS, such screening is still associated with a significant false positive and false negative rate as the detection rate is only 52% [6].

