We have recently reported significant differences in maternal serum between women with twin pregnancies complicated by TTTS, and twin pregnancies not complicated by TTTS but matched for gestational age [7]. These differences were seen in alpha-fetoprotein (αFP), β-hCG, plasma vascular endothelial growth factor (VEGF)-C, angiopoietin (Ang)-2 levels and the ratio of soluble vascular endothelial growth factor receptor-1 (sVEGFR-1) (also known as soluble fms-like tyrosine kinase-1. [sFlt-1]) to placental growth factor (PlGF) levels. We hypothesize that if these changes precede the development of the clinical syndrome, this may increase the sensitivity and specificity of detecting adverse pregnancy outcomes. The objective of this paper is to describe the aims and study design of our ongoing platform of work exploring complications in MC twin pregnancies.

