#### Prospective cohort

The prospective study will run over 2 years (August 2015–August 2017) and there will be 2 cohorts: a “screening” MC twin cohort (Cohort S), and a cohort who have developed complications (Cohort C) (see Fig. 1). In both cohorts, informed written consent will be obtained. The “screening” cohort (Cohort S) will be approached in the ‘multiples’ antenatal clinic where all twin pregnancies are managed at Birmingham Women’s NHS Foundation Trust. We will ask participants with confirmed MC twin pregnancies to consent to 2 extra bottles of blood being taken during their routine Down Syndrome blood test or booking blood tests, and for permission to record their first trimester ultrasound measurements, and access the above outcome data as specified in the retrospective study. We will then repeat the blood sampling at 16 weeks and 20 weeks gestation when they attend for routine ultrasound scans. If the participant does not develop any complications, this will be the end of her involvement in the study and we will just collect the outcome data. However, if she develops a complication (e.g. TTTS, TAPS, sIUGR, single intrauterine demise) she will be invited and consented to enter the second prospective “complicated” cohort.

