### Data management and data analyses

At recruitment, each participant will receive a unique study identifier to allow linkage of data. Data will be collected using a purposely designed proforma (as per the retrospective cohort) and manually input onto a secure electronic database. Hard-copies of data will be kept in a locked filing cabinet, in a swipe-card access department at Birmingham Women’s NHS Foundation Trust. We will ensure that we remain compliant with the Trust’s Information Governance policies at all times.

Descriptive data will be reported. First trimester ultrasound measurements (NT and CRL) and serial serum biomarkers will be compared between participants in cohort S who go on to develop complications, and participants in cohort S who do not develop complications. The serum biomarker results from the 16 and 20 week blood samples from participants in cohort S will also act as the control group for cohort C participants. Additionally serum and amniotic fluid biomarkers will be compared longitudinally (i.e. pre- and post-FLA) for each participant in cohort C, to evaluate the potential effect of FLA on the biomarkers. The appropriate statistical tests will be used. Chi-squared will be used for categorical variables, and student’s t-test (paired and unpaired where appropriate) for continuous variables. Logistic regression models will be created to assess the association between variables and outcomes and presented as odds ratios (OR) with a 95% confidence interval (CI). Different cut-offs will be used for TTTS (Quintero staging) and sIUGR (EFW <10^th^ centile, <5^th^ centile).

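### Cohort C is sampled at laser but its controls only at 16 and 20 weeks, and the t-test named for biomarkers has no gestation term, so this contrast can confound disease with gestational age

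*Protocol article*

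**What the plan says.** Under Methods, Prospective cohort (text following Fig. 1), the timing of case blood follows the procedure and not a gestational week: "The second cohort (Cohort C) will have serial maternal blood tests performed (pre-FLA and 6 h post-FLA"). Gestation at laser is not stated. The nearest figure is in the Background: "TTTS complicates 10–15% of MC twins and usually occurs between 15 and 26 weeks".

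For Cohort S, after the first-trimester sample, the Prospective cohort section says: "We will then repeat the blood sampling at 16 weeks and 20 weeks gestation when they attend for routine ultrasound scans". A woman without complications then gives no more blood; only her outcome data are collected.

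Data management and data analyses joins the two cohorts by giving Cohort C its comparator: "The serum biomarker results from the 16 and 20 week blood samples from participants in cohort S will also act as the control group". The test it names for continuous variables is Student's t-test ("paired and unpaired where appropriate) for continuous variables"). It adds logistic regression without naming covariates. Gestation at sampling is not mentioned. By contrast, the Background says the team's earlier work compared TTTS pregnancies with "twin pregnancies not complicated by TTTS but matched for gestational age".

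**The concern.** Cases are sampled at a variable gestation and controls at two fixed weeks. An unpaired t-test between them attributes the whole difference to disease. If a marker changes with gestation, the groups can differ with no disease effect, and the direction of the error depends on the marker and on which control visit is used.

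This bears on a stated aim, the effect of complications on angiogenic and placental growth factors in maternal blood. The comparison inside Cohort S is small for TTTS: 56 women × 10–15% gives about 6–8 affected pregnancies. The contrast of 40–60 Cohort C women with Cohort S therefore carries much of the weight. A larger sample would not remove the confounding; it would make a spurious difference more likely to reach significance.

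**Working it through.** **Stated figures.** Under Expected number of participants, Cohort S is 7,900 × 0.02 = 158; × 0.30 = 47.4; × 0.70 = 33.2; − 5 = 28.2; × 2 = 56.4 (stated as 56). Cohort C is 80–120 × 0.5 = 40–60. Both reproduce. No power calculation is given for this contrast.

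**Inputs from the article.** TTTS window 15–26 weeks (Background); control visits at 16 and 20 weeks (Prospective cohort; Data management and data analyses).

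**Assumptions.** Gestation at case sampling is uniform over the TTTS window, which stands in for gestation at laser. A marker rises by r = 5% or 10% per week; for a falling marker the direction reverses. There is no true disease effect.

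**Gap in gestation.** Mean case gestation is (15 + 26)/2 = 20.5 weeks. The share of the window after the last control visit is (26 − 20)/(26 − 15) = 6/11 = 55%.

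**Spurious ratio of geometric means** = (1 + r)^gap:

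| Control samples | Gap (weeks) | r = 5% | r = 10% |
|---|---|---|---|
| 20 weeks | 20.5 − 20 = 0.5 | 1.05^0.5 = 1.02 | 1.10^0.5 = 1.05 |
| Both pooled (mean 18) | 20.5 − 18 = 2.5 | 1.05^2.5 = 1.13 | 1.10^2.5 = 1.27 |
| 16 weeks | 20.5 − 16 = 4.5 | 1.05^4.5 = 1.25 | 1.10^4.5 = 1.54 |

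**Other timing.** If lasers centre on 18 weeks, the gap to pooled controls is 0 and the average bias vanishes. Against one visit the gap is 2 weeks either way: 1.05^2 = 1.10 to 1.10^2 = 1.21 against 16 weeks, and the reciprocals, 0.91 to 0.83, against 20 weeks.

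**False-positive rate of the t-test.** This was simulated with 4,000 replicates, two-sided alpha 0.05, 40 or 60 cases, 48 control women, a marker linear in gestation and no disease effect. When visits were pooled, the within-woman correlation was 0.5. All of these settings are assumptions except the case numbers. With uniform 15–26 week timing:

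| Slope (SD per week) | vs 16 weeks | vs 20 weeks | vs both pooled |
|---|---|---|---|
| 0 | 5% | 5–6% | 6–7% |
| 0.05 | 17–21% | 5% | 13–14% |
| 0.10 | 54–60% | 5–6% | 26–33% |
| 0.20 | 96–99% | 7% | 65–75% |

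The pooled column exceeds 5% at zero slope because two samples from one woman are treated as independent. With lasers uniform over 16–20 weeks, pooled rates stay at 6–7%, but a single-visit comparison at 0.10 SD per week still rejects in 15–18% of runs.

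**The case against.** The strongest reply is that a journal article is condensed. It does not expressly assign the unpaired t-test to this contrast, it promises suitable tests in general terms, and its regression could include gestation. Covariate lists and gestation-specific standardisation are often left to a fuller plan. That stands as far as it goes: the t-test is unadjusted, and the regression is unspecified rather than unadjusted.

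A reader might infer that the plan pools the two control visits, that a 13–27% bias is to be expected, and that 55% of cases lie beyond the controls. The article supports none of these. It does not say the visits are pooled, it gives no marker slope, and 55% is a share of the window in which TTTS usually occurs, not an estimate of when lasers are done. Against 20-week controls the bias could be slight.

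What the reply does not answer is the design. The control weeks are fixed in the article, no uncomplicated woman is sampled after 20 weeks, and no analysis plan can supply those samples. Adjustment for later cases would extrapolate. The article also names a control group and a test and gives no rule for choosing between visits, although the team's earlier comparison was matched for gestation.

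**Conclusion.** The concern holds for one contrast, Cohort C against Cohort S. As written, it can confound disease with gestational age. The size is unknown: under the uniform-timing and 5–10% per week assumptions it runs from about 2–5% (20-week controls) to 25–54% (16-week controls), and it is near zero for pooled controls if lasers centre on 18 weeks.

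It would be wrong to read this as undermining the whole study. The pre/post-laser comparison is within woman and spans hours. The comparison inside Cohort S uses common scheduled visits. The retrospective cohort and the first-trimester ultrasound aim do not use this contrast.

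**What to change.** In Data management and data analyses, replace the unpaired t-test for this contrast with a regression of log biomarker on group and gestational age at sampling. Use the pre-laser case sample against the control samples, with a random intercept for women who contribute more than one sample.

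Make the primary contrast the cases sampled within the gestational range the controls cover: about 16–20 weeks with a small prespecified margin. Report later cases only as a sensitivity analysis labelled as extrapolation. Keep every case in the pre/post-laser comparison. State that there are no controls after 20 weeks.

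The change is to wording and analysis, and needs only gestation at each sampling date. The cost is precision. On the uniform assumption, a 15+0 to 21+0 limit keeps 6/11 of cases: 40 × 6/11 = 22 to 60 × 6/11 = 33, a loss of about 45% from this one contrast. The fix does not create later controls, so disease effects in later cases would remain dependent on the model.

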### Expected number of participants

In the retrospective study cohort, these samples are routinely stored for 2 years and equate to approximately 170 samples in total.

Regarding the prospective cohort S: Birmingham Women’s NHS Foundation Trust has 7,900 deliveries per annum, approximately 2% of all maternities are multiple pregnancies and thus would equate to 158 maternities per annum. Of these, approximately 30% are MC twins (47 MC twins per annum) and 70% of women with an MC pregnancy will consent to Down syndrome screening (33 MC twins per annum). If we propose that 5 per year will be lost by miscarriage or decline participation in the study, then we predict recruitment of approximately 28 MC twin pregnancies per annum, which equates to 56 maternities over 2 years of proposed recruitment.

At the West Midlands Fetal Medicine Centre we treat approximately 40–60 women a year with TTTS, which equates to 80–120 women over 2 years. If we allow for a 50% recruitment rate and incomplete follow-up, results in 40–60 sets of parents participating over 2 years in cohort C.

### Data management and data analyses

At recruitment, each participant will receive a unique study identifier to allow linkage of data. Data will be collected using a purposely designed proforma (as per the retrospective cohort) and manually input onto a secure electronic database. Hard-copies of data will be kept in a locked filing cabinet, in a swipe-card access department at Birmingham Women’s NHS Foundation Trust. We will ensure that we remain compliant with the Trust’s Information Governance policies at all times.

Descriptive data will be reported. First trimester ultrasound measurements (NT and CRL) and serial serum biomarkers will be compared between participants in cohort S who go on to develop complications, and participants in cohort S who do not develop complications. The serum biomarker results from the 16 and 20 week blood samples from participants in cohort S will also act as the control group for cohort C participants. Additionally serum and amniotic fluid biomarkers will be compared longitudinally (i.e. pre- and post-FLA) for each participant in cohort C, to evaluate the potential effect of FLA on the biomarkers. The appropriate statistical tests will be used. Chi-squared will be used for categorical variables, and student’s t-test (paired and unpaired where appropriate) for continuous variables. Logistic regression models will be created to assess the association between variables and outcomes and presented as odds ratios (OR) with a 95% confidence interval (CI). Different cut-offs will be used for TTTS (Quintero staging) and sIUGR (EFW <10^th^ centile, <5^th^ centile).

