**Methods:**

This cohort study has retrospective and prospective elements. In the retrospective cohort we will measure factors (decided based on preliminary work and a systematic review and meta-analysis) in stored maternal blood samples taken in the first-trimester, extract first-trimester ultrasound measurements and match these to pregnancy outcome. The prospective cohort will be divided into a “screening” cohort and “complicated” cohort. The screening cohort will undergo serial maternal blood sampling at 12, 16 and 20 weeks; we will extract ultrasound measurements and match to pregnancy outcome. The complicated cohort will comprise of women referred to the Fetal Medicine Centre with complications of monochorionicity. If the decision is taken to undergo fetoscopic laser ablation we will take maternal blood samples and amniotic fluid samples pre- and post-laser treatment. The same factors will be measured in the prospective cohort as informed by the retrospective study.

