## Methods

### Aims of study

The aim of our research is to improve knowledge of complications in MC twin pregnancies, and incorporate this knowledge into a predictive model in the future. Specifically we will investigate:If abnormal first-trimester ultrasound measurements (NT and CRL) are associated with the development of complications later in pregnancy.The effects that these complications and their treatment have on:angiogenic factors in maternal serum/plasmaplacental growth factors in maternal serum/plasmaangiogenic factors in amniotic fluidplacental growth factors in amniotic fluid

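### Cohort S biomarkers are compared by eventual complication status without limiting each draw to women still undiagnosed, so a 20 week difference cannot by itself show that changes precede TTTS

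*Protocol article*

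**What the plan says.** All references are to the protocol article.

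- **Sampling.** The Abstract states: "The screening cohort will undergo serial maternal blood sampling at 12, 16 and 20 weeks". The Prospective cohort section adds: "We will then repeat the blood sampling at 16 weeks and 20 weeks gestation when they attend for routine ultrasound scans".
- **Onset.** The Background states: "TTTS complicates 10–15% of MC twins and usually occurs between 15 and 26 weeks".
- **Comparison.** Data management and data analyses states that "serial serum biomarkers will be compared between participants in cohort S who go on to develop complications" and cohort S women who do not. The listed tools are t-tests, chi-squared tests and logistic regression. No timing relative to diagnosis is mentioned.
- **Second use.** The same section makes the 16 and 20 week results of cohort S participants the control group for cohort C, with no limit to uncomplicated women.
- **What happens at onset.** On developing a complication, "she will be invited and consented to enter the second prospective “complicated” cohort". The Discussion expects some women to be in both cohorts.
- **Purpose.** The Background reads: "We hypothesize that if these changes precede the development of the clinical syndrome", detection of adverse outcome may become more sensitive and specific. The biomarker item under Aims of study is framed differently: "The effects that these complications and their treatment have on" angiogenic and placental growth factors in maternal blood and amniotic fluid.

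**The concern.** The groups are defined by what eventually happens to a woman, not by her status on the day of the sample. At 12 weeks the two coincide for TTTS, because the draw comes before the stated window. At 20 weeks they do not: the draw falls well inside the window, and some women in the complication group may already be diagnosed or may already have had fetoscopic laser ablation (FLA). The repeat draws are taken at routine scans, so a diagnosis on the day of sampling is foreseeable.

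The Background reports that biomarker differences in established TTTS have already been found. A 20 week contrast that mixes pre-onset and established cases could reproduce that known result and be taken for an early signal. Post-laser samples could move it in either direction, and the article itself plans to test whether FLA changes the biomarkers. The mixture also serves the aim on effects of complications poorly, because the pre-onset samples dilute that effect.

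The use of cohort S samples as controls has the same gap. As written, an affected woman's 20 week sample could sit in the control group for cohort C.

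**Working it through.** **Inputs from the article:** 7,900 deliveries a year, 2% multiple, 30% of those monochorionic, 70% accepting Down syndrome screening, 5 a year lost or declining, two years (Expected number of participants); TTTS in 10–15%, usual onset at 15 to 26 weeks (Background).

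**Cohort S size.** 7,900 × 0.02 = 158; × 0.30 = 47.4; × 0.70 = 33.2; − 5 = 28.2 a year; × 2 = 56.4. This reproduces the stated 56. The article gives no power calculation to reproduce.

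**Expected TTTS cases.** 56 × 0.10 = 5.6; 56 × 0.15 = 8.4.

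**Share with onset by each draw.** The article gives no onset distribution. Assuming uniform onset over the window, the share is (week − 15)/(26 − 15).

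| Draw | Share with onset | Cases with onset | Cases still pre-onset |
|---|---|---|---|
| 12 weeks | 0 | 0 | 5.6 to 8.4 |
| 16 weeks | 1/11 = 9% | 0.5 to 0.8 | 5.1 to 7.6 |
| 20 weeks | 5/11 = 45% | 2.5 to 3.8 | 3.1 to 4.6 |

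If the share by 20 weeks is instead 20% to 70% (an assumed range), the cases with onset run from 5.6 × 0.20 = 1.1 to 8.4 × 0.70 = 5.9.

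**What a mixture can do.** As an illustration, assume no difference before onset and a shift of 1, 1.5 or 2 SD after it. The apparent difference is the share times the shift. An unpaired t-test at nominal 5% was simulated 20,000 times per setting, with 6 cases against 50 controls and 8 against 48.

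| Share post-onset | Apparent difference (1 / 1.5 / 2 SD) | Rejection rate (1 / 1.5 / 2 SD) |
|---|---|---|
| 9% (16 weeks, uniform) | 0.09 / 0.14 / 0.18 SD | 6% / 8% / 10% |
| 20% | 0.20 / 0.30 / 0.40 SD | 9% / 13–15% / 19–21% |
| 45% (20 weeks, uniform) | 0.45 / 0.68 / 0.91 SD | 20–23% / 35–40% / 50–57% |
| 70% | 0.70 / 1.05 / 1.40 SD | 37–43% / 63–72% / 80–88% |

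The 20 week comparison could thus show a difference with no pre-onset change at all. At 16 weeks the distortion is slight. The shift sizes are assumptions; the article gives no biomarker effect sizes or SDs.

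**Limits.** These figures cover TTTS only. The stated comparison groups women by any complication, and the article gives no onset timing for selective growth restriction, twin anaemia polycythaemia sequence or fetal demise. The affected share of the full case group is therefore unknown. The counts also assume that a diagnosed woman still gives her later cohort S sample.

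**The case against.** The tempting stronger reading is that the study counts post-onset samples as evidence that changes precede the syndrome. The article does not say this. It nowhere states that post-onset samples stay in the cohort S comparison, and it draws no conclusion about precedence from the 16 or 20 week data. The wording about women who go on to develop complications suggests later onset, and an affected woman is invited into cohort C, which has its own draws around FLA. The timing hypothesis is conditional, the biomarker aim concerns effects of complications, and the Discussion concedes that numbers are too small to develop a prediction model. All of this stands, and it rules out the stronger reading.

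Nor can a reader infer that the precedence question as a whole is compromised. The 12 week samples and the roughly 170 retrospective first-trimester samples come before the TTTS window. Nor should the 16 and 20 week draws be treated alike.

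The remaining objection is that sample eligibility is detail for a fuller protocol or analysis plan, which may contain such a rule. That carries only part of the way. The article does define the groups, by eventual status, and applies them to the whole series. For one such group across three draws, later onset is assured for TTTS only relative to the first. An invitation into cohort C does not remove a woman from cohort S, and the Discussion expects overlap. Followed as written, the comparison allows the mixture.

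**Conclusion.** The point holds in limited form. The stated comparison does not separate women undiagnosed at a draw from those already affected or treated. A 20 week difference therefore cannot by itself support the claim that biomarker changes precede TTTS. Under uniform onset, 2.5 to 3.8 of 5.6 to 8.4 expected TTTS cases would already have begun by 20 weeks (1.1 to 5.9 for a share of 20% to 70%). The 16 week problem is marginal, at 0.5 to 0.8 of a case. For TTTS, the 12 week and retrospective first-trimester comparisons are unaffected. The size rests on the assumed onset distribution and on diagnosed women still giving cohort S samples. For the other complications it cannot be stated.

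**What to change.** Replace the eventual-status comparison with a landmark rule at each draw:

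1. At 12, 16 and 20 weeks, include only women with no diagnosed complication and no FLA at that draw, and compare those diagnosed later with those never diagnosed.
2. Report samples taken at or after diagnosis separately, as established disease, and give the interval from sample to diagnosis.
3. Restrict the 16 and 20 week cohort S controls for cohort C to women without a complication.

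This needs no extra sampling, only the date of diagnosis, which routine scans should supply, and a change to the analysis wording. The cost is precision at 20 weeks: about 3.1 to 4.6 TTTS cases would remain in the pre-onset comparison under uniform onset, instead of 5.6 to 8.4, so intervals will be wider. If a fuller protocol or analysis plan already contains such a rule, stating it alongside the comparison is enough.

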## Discussion

This study aims to increase knowledge surrounding the pathology of complications in MC twins, which in turn is hoped to aid future diagnosis and management. To our knowledge, this is the first study to look at these serum and amniotic fluid biomarkers in such a large cohort of MC twin pregnancies.

Although we are one of the largest Fetal Medicine Centres in the UK, the number of participants eligible for inclusion is insufficient to power the development of a prediction model, and may cause false negative results. The results of this study may inform a larger, multi-centre study to be conducted over several years so as to create a prediction model to triage MC twin pregnancies as high-risk or low-risk for complications, and thus requiring more or less surveillance antenatally.

There will be some women who will have booked at Birmingham Women’s NHS Foundation Trust and will be recruited to both the first-trimester screening cohort and the “complicated” cohort. Parents are routinely informed of the potential complications of MC pregnancy at booking, and by seeing these women in the first-trimester, this will give us the opportunity to inform them of the second part of the prospective study and they will have at least 4 weeks to consider participation should a complication develop. However, as a tertiary Fetal Medicine Centre we receive a lot of referrals from around the UK for second opinions and to perform treatment for MC twin complications, e.g. FLA. These referred patients will also be eligible for inclusion in the “complicated” cohort, although we will not have first-trimester blood samples for them. Unfortunately, due to the rapid progression of complications, these parents may have a limited time to consider participation. However, this is still in-keeping with ethical approval.

Although we will be unable to gain consent for participants in the retrospective study, we intend to publish our results on the TAMBA website to which the public have access. We also hope to present them at international conferences and publish in leading medical journals.

We expect to lose some participants to follow-up, and to be unable to collect outcome data for some patients who may have moved areas, or have had their baby(ies) transferred out to different neonatal units.

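### The serum controls for cohort C are all of cohort S, so they include women who develop complications and some women who are also cohort C cases

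*Protocol article*

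**What the plan says.** Data management and data analyses defines the comparison group for cohort C in one sentence, which concerns the serum results at 16 and 20 weeks: "blood samples from participants in cohort S will also act as the control group for cohort C participants". No condition on pregnancy outcome is attached. The sentence just before it does make that distinction, for a different comparison: it contrasts "participants in cohort S who go on to develop complications, and participants in cohort S who do not develop complications".

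Two other places say that the cohorts share women. Under Prospective cohort, a cohort S participant who develops a complication such as TTTS, TAPS, sIUGR or single demise stays in view: "she will be invited and consented to enter the second prospective “complicated” cohort". The Discussion confirms that some women booked at the study hospital "will be recruited to both the first-trimester screening cohort and the “complicated” cohort". Nothing in the article removes these women from the control group or says how the overlap is analysed.

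Expected number of participants puts cohort S at "approximately 28 MC twin pregnancies per annum, which equates to 56 maternities over 2 years of proposed recruitment", and cohort C at 40–60.

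**The concern.** A control group for complicated pregnancies should show what the biomarkers look like without the complication. Under the stated rule it is a mixture of mostly unaffected women and some who have, or will have, the condition that defines the cases. If the affected women's samples have already moved towards the case level, the control mean moves with them and the case-control difference shrinks. The study's own hypothesis, in the Background, is that biomarker changes may come before the clinical syndrome. If that is right, this dilution follows.

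The second problem is overlap. A woman who moves from S to C contributes to both sides of the comparison. An unpaired test treats the two groups as independent, and for her they are not.

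The Discussion already warns that the numbers may produce false negative results. This rule adds an avoidable cause. It also departs from the earlier work that the study follows up, which the Background describes as comparing TTTS with gestation-matched twin pregnancies free of TTTS.

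**Working it through.** **Reproducing the stated sizes** (Expected number of participants)

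- Cohort S: 7,900 × 2% = 158; × 30% = 47.4; × 70% = 33.2, rounded to 33; minus 5 = 28 a year; × 2 = 56. This agrees with the article.
- Cohort C: 40–60 a year × 2 = 80–120; × 50% = 40–60. This agrees.

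**Affected women among the controls**

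- The Background gives TTTS in 10–15% of MC twins. 56 × 0.10 = 5.6 and 56 × 0.15 = 8.4, so about 6–8 women.
- If the 50% used for cohort C also applied to them (an assumption), 2.8–4.2, or about 3–4 women, would be on both sides.
- If all of them entered cohort C, they would be 5.6/60 = 9% to 8.4/60 = 14% of a cohort of 60, and 5.6/40 = 14% to 8.4/40 = 21% of a cohort of 40.

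**Dilution**

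Let f be the share of controls who are affected and g the fraction of the case shift already present in their 16 and 20 week samples. The expected difference is δ × (1 − f × g). The article gives no effect size, so δ = 0.50 SD is illustrative. The percentage loss, f × g, does not depend on it.

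| g | f = 10% | f = 15% |
|---|---|---|
| 1 (full shift) | 0.450 SD (−10%) | 0.425 SD (−15%) |
| 0.5 (half shift) | 0.475 SD (−5%) | 0.4625 SD (−7.5%) |
| 0 (no shift yet) | 0.50 SD (0%) | 0.50 SD (0%) |

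TAPS, sIUGR and demise would raise f, but the article gives no overall rate. At an assumed 20–40%, 11–22 of the 56 would be affected. The difference would then be 0.40–0.30 SD at full shift and 0.45–0.40 SD at half shift.

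**What restriction costs in precision**

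Removing 6–8 women leaves 50–48 controls. With unit SD, SE = √(1/n_C + 1/n_S).

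- 40 cases: √(1/40 + 1/56) = 0.2070 with all of S; 0.2121 with 50 controls (+2.5%); 0.2141 with 48 (+3.4%).
- 60 cases: √(1/60 + 1/56) = 0.1858 with all of S; 0.1915 with 50 controls (+3.1%); 0.1936 with 48 (+4.2%).

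At half shift or more, the signal lost by keeping the affected women (5–15%) exceeds the precision lost by removing them (2.5–4.2%). With no shift, removal costs that small loss of precision and gains only the end of the overlap. This comparison ignores the slightly larger variance of a mixed control group and the covariance due to shared women.

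**The case against.** **Timing.** TTTS usually arises between 15 and 26 weeks, so many of the 16 and 20 week samples, especially the earlier ones, may precede onset. Whether the biomarkers move before onset is the question under study. This stands. A reader might infer that every cohort C versus S contrast shrinks by the full share of complicated women. The article supports that only as the upper end of a range that starts at zero.

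**Size of the overlap.** Entry to cohort C needs a separate consent, and its sampling is described around laser treatment, so few women would appear twice. This also stands. Few is not none, however, and no rule covers them.

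**Repeated values.** A reader might infer that the 16 and 20 week results are pooled in one unpaired t-test, treating two values from one woman as independent. The article does not say so. It names paired and unpaired t-tests as appropriate, and two control time points could equally serve as separate gestation-specific comparators. This is a condition to meet if they are analysed together, not an error in the plan.

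**Choice of control.** Requiring controls to stay uncomplicated selects on later outcome. A woman not yet diagnosed at 16 weeks could be a legitimate control in a design that samples those still at risk, and the earlier work excluded only TTTS. That design is defensible if it is stated, but the article does not describe it. The article already uses an uncomplicated group in the preceding sentence.

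**A condensed document.** A full protocol or SAP may restrict the controls, and the figure is not shown. But the article does more than leave the point open: it names the control group, and names it without restriction. Nor can the wording be read as women leaving cohort S once complicated, because the preceding sentence still calls them cohort S participants.

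**Conclusion.** The concern holds in a limited form. The control group as stated overlaps with the cases and includes affected women. On TTTS alone that is about 6–8 of 56 controls, with about 3–4 also in cohort C at 50% recruitment. The dilution is 10–15% of the true difference at full shift, 5–7.5% at half shift, and zero for a biomarker that has not yet moved. It rests on two quantities that the article does not give: how much of the shift is present at 16 and 20 weeks, and the complication rate beyond TTTS.

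A reader might infer a severe loss of power. The documents do not support a figure for this: they state no effect size, alpha or power for this contrast, and the larger losses shown above depend on an assumed overall complication rate.

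The fault is confined to the serum comparison of cohort C with cohort S. The comparison within cohort S by complication status and the comparison before and after laser within cohort C do not use this control group. In an exploratory study this is a should-fix.

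**What to change.** In Data management and data analyses, restrict the serum controls for cohort C to cohort S women who do not develop a listed complication, which is the group already defined in the sentence before. State that women who enter cohort C count as cases only in this contrast, and that their earlier cohort S samples are used in a within-woman comparison. If the 16 and 20 week values are analysed together, allow for two values per woman, for example with a random intercept for woman, or use one value each.

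The cost is one or two sentences and no new data, since pregnancy outcomes are already collected for all of cohort S. The control group loses about 6–8 women on TTTS alone, leaving about 48–50, and more once the other complications are counted (11–22 lost and about 34–45 left at an assumed 20–40%). Control status is known only once outcome is known, so women without outcome data will need a stated rule.
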